#### **6.1.1. Study populations**

Only patients with a diagnosis coded with a final digit according to ICD: C00 - C14, C30 - C32 Malignant neoplasms of the lip, oral cavity, pharynx, upper respiratory tract ("head and neck tumours") are included. No persons requiring special protection are included.

#### **6.1.2. Description of the patient collective**

If possible, men and women should be included in the study in the same proportion. Antineoplastic therapy (radiotherapy, surgery, chemotherapy or immunotherapy) must have been completed for at least 4 months (or after completion of follow-up treatment).

#### **6.1.3. Primary outcome**

This study consists of two phases.

Phase A (feasibility & quality of life, n = 25):

The hypothesis is tested that the proportion of patients completing the training intervention in the home-based setting over 12 weeks is  $\geq 70\%$ .

Phase B (quality of life, n = 35, total n = 60):

The hypothesis will be tested that the global QoL score (EORTC-QLQ-30) will increase significantly after a 12-week training intervention in the home-based setting.

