A total of 12 patients (6 male, 6 female,  $68 \pm 9$  years) were included in the study. Ten (83%) completed the study successfully. The attendance rate of the participants was 83% ( $20 \pm 3$  of 24 units). The functional tests showed various significant improvements in the range of motion (ROM) of the shoulder joints and the cervical spine. At the end of the intervention, all participants scored full marks in the Short Physical Performance Battery (SPPB, test includes balance, leg strength and walking speed). In the 6-minute walk test, patients covered an additional distance of 43 metres (+8.3%) after the intervention, whereby the subjective perception of exertion was significantly lower. In order to evaluate changes in QoL, the EORTC-QLQ-30 and EORTC H&N35 questionnaires were completed by the participants before and after the intervention. The analysis showed a trend towards an improvement in global QoL ( $p = 0.059$ ). The effect size corresponds to a medium effect ( $d = 0.626$ ). Positive changes were seen in three of the five functional scales of the EORTC-QLQ-30: physical function (+6.7 points,  $p = 0.008$ ,  $d = 1.077$ ), cognitive function (+48.3 points,  $p = 0.015$ ,  $d = 0.829$ ) and social function (+23.4 points,  $p = 0.031$ ,  $d = 0.604$ ). There were no statistically significant changes in the three symptom scales and six single items. In the symptom scales of the H&N35, only sexuality showed a significant improvement (-16.5 points,  $p = 0.031$ ,  $d = 0.928$ ). The "social contact" scale showed a tendency towards improvement (-8.6 points,  $p = 0.68$ ,  $d = -0.542$ ) [17,18].

The good compliance of the participants, the positive effects in terms of physical functionality and QoL provide an excellent basis for the transfer to a home training programme (home-based setting).

As part of the pilot study, an "Exercise manual for patients with mouth, jaw, face and neck tumours" was written (ISBN: 978-1099096082 ). It contains a total of 90 mobilisation, coordination, strengthening and stretching exercises for training at home. Videos of the exercises have been created to accompany the book. Both the book and the videos will be made available to the HNSCC patients participating in the study for independent practice at home.

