#### **4.6.3. Data analysis**

This study is a prospective longitudinal study. The data will be analysed by estimating the drop-out rate, descriptive statistics, correlation tests (correlation and regression analysis) and multifactorial methods for testing differences (e.g. analysis of variance with repeated measures). The data will be analysed in cooperation with the IBIMA of the UMR.

The evaluation with regard to phase I (feasibility) will take place after 25 patients have been included in the study. In addition, ad hoc analyses will be performed. In the case of rapid recruitment, this will be paused at 60 patients included in the study and, if necessary, continued depending on the results of the analyses.

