## **6. Statistical methods and determination of the sample size**

### **6.1. Statistical and analytical plan**

The drop-out rate is estimated to determine the primary outcome of phase A (feasibility).

The statistics of the primary and secondary outcomes (phase B) include: descriptive statistics, calculation of the mean individual differences and testing for zero; t-test for dependent samples/Wilcoxon/McNemar), distribution test for equality  $\chi^2$ -test; risk assessment or determination of association measures and testing for zero; correlation/regression and analysis of variance with repeated measures.

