## **6.2. Determination of the sample size**

The case number calculation of phase I is based on the calculation that with  $n = 24$ , a 30% dropout rate can be estimated with an accuracy of  $\pm 18\%$  at a confidence level of  $1 - \alpha = .95$  (2-sided) (nQuery® Advisor 7.0 Statistical Solutions Ltd., Boston, MA, USA).

The sample size calculation for the trial (phase B) is based on the results of Felser et al. (28): global QoL pre:  $50.1 \pm 16.4$ ; post:  $58.3 \pm 16.2$ ;  $r = 0.618$  resulting in an effect size of 0.5755, which is detectable on a confidence level of  $1 - \alpha = .95$  (2-sided) with  $n = 42$  patients (nQuery® Advisor 7.0 Statistical Solutions Ltd., Boston, MA, USA). Assuming a 30% dropout rate based on our experience, a total of  $N = 60$  patients is required to be included in the study.

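### Phase A is worded as a test that completion is at least 70%, but it is planned and sized only to estimate a rate centred on 70%, so the pass mark depends on how the sentence is read

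*Protocol*

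**What the plan says.** Section 2.4 defines the Phase A primary outcome as the percentage of patients who complete the 12-week home training. Three places then say how it is handled.

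- Section 6.1.3, under "Phase A (feasibility & quality of life, n = 25", gives a test: "The hypothesis is tested that the proportion of patients completing the training intervention in the home-based setting over 12 weeks is" at least 70%.
- Section 6.1 gives an estimate: "The drop-out rate is estimated to determine the primary outcome of phase A (feasibility"). The tests listed there are for the Phase B primary outcome and the secondary outcomes.
- Section 6.2 gives a precision calculation. With n = 24, "a 30% dropout rate can be estimated with an accuracy of" ±18%, at 95% two-sided confidence. It calls the phase by another label ("The case number calculation of phase I is based on the calculation that with" this n), but it is the feasibility phase: section 4.6.3 uses the same label, "The evaluation with regard to phase I (feasibility) will take place after 25 patients have been included in the study".

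For Phase A the protocol states no direction of the null hypothesis, no test level, no alternative rate, no power and no pass count.

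**The concern.** A test needs a null value and a different rate at which it is meant to succeed. Here the planning rate (30% dropout, so 70% completion) and the threshold (70%) are the same number. If the planning assumption is right, no test against 70% can reliably tell success from failure.

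The sentence in 6.1.3 can also be read in more than one way, and the readings give very different pass marks. At stake is the conclusion on one of the two declared primary outcomes: a middling result could be called feasible or not feasible according to a reading chosen after the data are seen.

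**Working it through.** **Inputs.** Threshold 70% and n = 25 (section 6.1.3). Dropout 30%, ±18 points, 95% two-sided, n = 24 (section 6.2). Pilot completion 10 of 12: "Ten (83%) completed the study successfully" (section 2.2).

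**1. The plan's own figure.** The half-width is 1.96 × √(0.30 × 0.70 / n).

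- n = 24: 1.96 × √(0.21/24) = 0.183
- n = 25: 1.96 × √(0.21/25) = 0.180
- n for exactly ±0.18: 1.96² × 0.21 / 0.18² = 24.9

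The stated ±18 points reproduces to within one patient. As an estimation target, the sizing is sound.

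**2. Pass marks.** X is the number of completers among 25, binomial, with the boundary at 0.70.

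- *70% is kept unless rejected.* P(X ≤ 13) = 0.044 and P(X ≤ 14) = 0.098. At one-sided 5%, 13 or fewer rejects, so 14 or more passes.
- *The observed proportion is compared with 70%.* 0.70 × 25 = 17.5, so 18 or more passes.
- *Completion above 70% must be shown.* P(X ≥ 22) = 0.033 and P(X ≥ 21) = 0.090. At one-sided 5%, 22 or more passes.

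**3. Sensitivity to the test level.** The only level the protocol gives for this phase is the 95% two-sided confidence of the interval, so one-sided 5% is an assumption.

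- A two-sided 5% score test gives the same cut-offs. For 13 and for 22 of 25, z = (x/25 − 0.70) / √(0.21/25) = −1.964 and +1.964, both just beyond ±1.960.
- Exact two-sided 95% limits (2.5% per tail) move them to 13 and 23, since P(X ≤ 12) = 0.017 and P(X ≥ 23) = 0.009.

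**4. Probability of passing, exact binomial, n = 25.**

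| Rule | true 50% | true 60% | true 70% | true 80% | true 83% |
|---|---|---|---|---|---|
| ≥13 | 50% | 85% | 98% | >99% | >99% |
| ≥14 | 34.5% | 73% | 96% | >99% | >99% |
| ≥18 | 2% | 15% | 51% | 89% | 95% |
| ≥22 | <1% | <1% | 3% | 23% | 36% |
| ≥23 | <1% | <1% | 1% | 10% | 18% |

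**5. How often the reading decides.** The first and third readings (cut-offs 14 and 22) disagree for every count from 14 to 21. At a true 70% the probability of such a count is 0.956 − 0.033 = 0.92.

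**6. What 25 patients can show.** At 18 of 25 (72%) the exact 95% interval is 50.6% to 87.9%, with 70% well inside it. Under the ≥22 rule even a true 90% passes only 76% of the time.

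**The case against.** The strongest reply is that the protocol, taken as a whole, already points to the middle reading. Section 2.4 defines the outcome as a percentage, 6.1 estimates it and 6.2 sizes for interval width. Comparing the observed percentage with 70% is then the natural rule, and only one verb in 6.1.3 is out of place. Much of this stands. A reader might infer that the verdict must be either 14 or 22 of 25, so that Phase A is uninformative whatever happens. The documents do not support that: the 18 of 25 reading is open and fits the rest of the text best. The protocol does not adopt it, however. It says a hypothesis is tested.

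A second reply is that the direction of the null, the test level and the pass count belong in a statistical analysis plan, which is not shown. Their absence alone is not the point. The protocol itself states a test in one section, and in two others plans and sizes for something else. An analysis plan could choose a test, but it could not make 25 patients adequate for one centred on the planning rate.

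A third reply concerns weight. A reader might infer that a wrong Phase A verdict would wrongly stop or continue the study. The text does not say so. Section 4.6.3 schedules an evaluation at 25 patients and, if recruitment is rapid, a pause at 60; section 8.1.1 asks only for an interim report. No enrolment decision is tied to the 70% figure, and the observed rate with its interval can be reported under any reading. This reply stands and limits the severity.

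Finally, the 18 of 25 rule itself passes only 51% of the time at a true 70%. That is unavoidable when the threshold equals the true rate, and it should be disclosed.

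**Conclusion.** The inconsistency is real. Section 6.1.3 announces a test against 70% that 6.1 does not plan and 6.2 does not size. Depending on the reading, the pass mark is 14 (or 13), 18, or 22 (or 23) of 25. At the planning rate of 70% the chance of passing is 96% (98%), 51% or 3% (1%) respectively. The lenient rule of 14 passes 73% of the time at a true 60%; the strict rule of 22 passes only 36% of the time at the pilot's 83%.

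These figures assume independent patients with a common completion probability and all 25 in the denominator. The cut-offs of 14 and 22 further assume one-sided 5% exact tests or a two-sided 5% score test. The 83% comes from 12 patients trained under supervision in small groups, so it is only a reference value for home training.

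Severity: should be fixed. The conclusion on a declared primary outcome is affected; enrolment and the Phase B analysis are not.

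**What to change.** In 6.1.3, replace the hypothesis test by estimation of the completion proportion in the 25 Phase A patients with an exact 95% confidence interval, in line with 6.1 and 6.2. Fix the feasibility criterion before any Phase A result is seen: an observed proportion of at least 70%, that is, at least 18 of 25.

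State the operating characteristics of that rule beside it: probability of meeting it 2%, 15%, 51%, 89% and 95% at a true completion of 50%, 60%, 70%, 80% and 83%. Add that 25 patients cannot demonstrate true completion above 70% unless it is far higher.

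As an option, report completion in all 60 patients as a supplementary estimate; at 70% its half-width is 1.96 × √(0.21/60) = 11.6 points.

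The cost is rewording of 6.1.3 and 6.2, with no extra patients. The downside is that Phase A no longer claims a confirmatory test of 70%.

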#### **6.1.4. Secondary outcomes**

Due to the complexity of the study, there are several secondary outcomes, which are listed below:

- Reasons for premature discontinuation of the 12-week training intervention
- Frequency and duration of training in the home-based setting on average per week (training volume)
- Medium-term change in QoL after a 12-week training intervention in the home-based setting
- Short-term change in mobility after a 12-week training intervention in the home-based setting

- Medium-term change in mobility after a 12-week training intervention in a home-based setting
- Short-term change in physical activity after a 12-week training intervention in a home-based setting
- Medium-term change in physical activity after a 12-week training intervention in a home-based setting
- Short-term change in balance ability/gait safety after a 12-week training intervention in a home-based setting
- Medium-term change in balance ability/gait safety after a 12-week training intervention in a home-based setting
- Short-term change in aerobic endurance capacity after a 12-week training intervention in a home-based setting
- Medium-term change in aerobic endurance capacity after a 12-week training intervention in a home-based setting
- Short-term changes in body composition after a 12-week training intervention in a home-based setting
- Medium-term changes in body composition after a 12-week training intervention in a home-based setting
- Correlations between the training volume during the 12-week training intervention and the effects with regard to QoL
- Correlations between the training volume during the 12-week training intervention and the effects on functionality
- Correlations between the training volume during the 12-week training intervention and the effects on body composition
- Relationships between daily activity and QoL
- Relationships between daily activity and functionality
- Correlations between daily activity and body composition
- Differences in the perception of the subjective effects of home training depending on gender

#### **6.1.5. Subgroup analyses**

Effects of the home-based intervention on QoL, functionality and physical activity will be analysed by means of subgroup analyses depending on gender and training volume.

## **6.2. Determination of the sample size**

The case number calculation of phase I is based on the calculation that with  $n = 24$ , a 30% dropout rate can be estimated with an accuracy of  $\pm 18\%$  at a confidence level of  $1 - \alpha = .95$  (2-sided) (nQuery® Advisor 7.0 Statistical Solutions Ltd., Boston, MA, USA).

The sample size calculation for the trial (phase B) is based on the results of Felser et al. (28): global QoL pre:  $50.1 \pm 16.4$ ; post:  $58.3 \pm 16.2$ ;  $r = 0.618$  resulting in an effect size of 0.5755, which is detectable on a confidence level of  $1 - \alpha = .95$  (2-sided) with  $n = 42$  patients (nQuery® Advisor 7.0 Statistical Solutions Ltd., Boston, MA, USA). Assuming a 30% dropout rate based on our experience, a total of  $N = 60$  patients is required to be included in the study.

## 7. Safety

To date, there is little data available on the occurrence of adverse events (AEs) in the routine care of oncological patients. To date, the occurrence of AEs in the training of oncological patients has mainly been recorded in the context of clinical studies. Based on previous results, training with oncological patients is considered to be feasible and safe [19,20], as the probability of an "adverse event" occurring can be considered low [21].

No medication is administered as part of this study. All examinations as part of the performance diagnostics are non-invasive. The training takes place in a home-based setting. The recommended exercises are adapted to the individual patient's state of health and current performance capacity. The training times, training volume and training intensity are determined independently by the study participants. It is expressly pointed out that training should not be carried out in the event of nausea/vomiting, severe pain, impaired consciousness and confusion, dizziness, circulatory problems, fever > 38° or severe infection. Nevertheless, incidents (e.g. nausea/vomiting, muscular complaints, circulatory problems) cannot be ruled out due to the unaccustomed strain.

In order to record any incidents that may occur, the patients are called once a week by the local therapist during the home-based intervention and the status quo is enquired about and incidents that were supposedly related to the home-based training are documented. A distinction is made between AEs and SAEs.

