#### 7.1.1. Adverse event (AE)

„These are health incidents that lead to a short-term impairment of physical functioning or health and are at most clarified by a doctor, but do not require treatment" [21].

The AE does not necessarily have to be causally related to the training. All events that occur during training (including performance diagnostics) are recorded as AEs.

AEs include, for example, dizziness, nausea or vomiting occurring during training or performance diagnostics. They also include sprains, ligament strains, torn muscle fibres and the like caused by training.

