#### 7.1.2. Serious adverse event (SAE)

"These are health incidents during training that result in a medium or long-term impairment of physical functioning or health and result in medical treatment (death, cardiac arrest requiring resuscitation, broken bones, incisional fractures and injuries)." [21]

SAEs during the performance of the study are incidents that are

- a) are fatal or life-threatening,
- b) require unscheduled hospitalisation and/or

c) require medium-term health impairment with medical treatment (e.g. conventionally treated bone fracture)

The SAE does not necessarily have to be causally related to the training. Events are considered life-threatening in the above context if there was a risk of death at the time of the event.

Any inpatient stay of a study participant that lasted at least one night (10 pm - 6 am) is considered a hospitalisation.

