## **7.2. Documentation and tracking of AEs/SAEs**

During the 12-week training intervention, which takes place in a home-based setting, all study participants are called once a week by their local therapist. The therapist asks about any adverse events (AEs and SAEs) that occurred during the training programme and documents these in a "telephone log" (Appendix 8). It should also be recorded during which the event occurred (endurance training, strength training, balance training, etc.).

After completion of the training intervention, the protocols are sent to the study management/study centre of the UMR, where all documented AEs/SAEs are collated.

During the follow-up period (12-week follow-up), the study participants inform their therapist of any incidents that occurred during training. In such cases, the therapist notifies the study centre of Clinic III, Haematology, Oncology and Palliative Medicine at UMR by fax or e-mail after being informed.

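### Section 7 ties documentation on the weekly call to presumed relation with training, 7.1.1 and 7.1.2 do not require relation, and 7.1.2 gives SAEs two time windows, so the safety count depends on which sentence a site follows

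*Protocol*

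**What the plan says.** Five places in the Protocol govern which events are written down.

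- **Section 7, Safety.** The sentence on the weekly call opens with a wide purpose, "In order to record any incidents that may occur", and ends with a narrower rule: "incidents that were supposedly related to the home-based training are documented".
- **Section 7.1.1, AE.** Relation is not a condition: "The AE does not necessarily have to be causally related to the training". The window is set by "All events that occur during training (including performance diagnostics) are recorded as AEs". The examples then bring cause back in for injuries: "They also include sprains, ligament strains, torn muscle fibres and the like caused by training".
- **Section 7.1.2, SAE.** The definition taken from the literature begins "These are health incidents during training that result in a medium or long-term impairment of physical functioning or health". The protocol's own list follows, introduced by "SAEs during the performance of the study are incidents that are", and includes unscheduled hospitalisation. The section then says that an SAE, too, need not be caused by training, and that an inpatient stay of at least one night counts as hospitalisation.
- **Section 7.2, Documentation and tracking.** On the weekly call the therapist asks about "any adverse events (AEs and SAEs) that occurred during the training programme". In follow-up, participants report incidents that happened in training.
- **Section 4.1, general design.** The weekly call covers adverse events in training, with no relation condition.

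**The concern.** The issue is which events are captured, not how they are graded. If presumed relation is applied before anything is written down, events that 7.1.1 and 7.1.2 count do not reach the log. If sites read the SAE window differently, the same admission is an SAE at one site and nothing at another.

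This matters because the study is single-arm and multicentre, training is done at home, and local therapists keep the record. No control group gives a background rate to set the count against. The call logs go to the study centre only after the 12 weeks, so an event that was left out may not be noticed. An analysis plan cannot repair a collection rule after the fact. A relation filter also works in one direction: it can only remove events, so it makes the programme look safer.

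**Working it through.** The Protocol states no AE or SAE rate and no figure on this point, so there is no plan figure to reproduce. The check sets the rules side by side and runs test cases through them.

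**Rules by section**

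| Place | Is relation to training required? | Time window |
|---|---|---|
| 4.1, weekly call | No condition stated | During training |
| 7, purpose of the call | No | None stated |
| 7, documentation on the call | Yes, presumed relation to home training | None stated beyond the calls in the 12 weeks |
| 7.1.1, AE | No | During training, including performance diagnostics |
| 7.1.2, cited SAE definition | See next row | During training |
| 7.1.2, protocol's own SAE list | No (the sentence follows the list and is about SAEs in general) | Conduct of the study |
| 7.2, weekly call | No condition stated | The training programme: either the sessions or the 12 weeks |
| 7.2, follow-up | No condition stated | During training, reported by the participant |

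**What the table shows**

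1. On relation, the documentation clause in Section 7 conflicts with 7.1.1 and 7.1.2, with the descriptions of the call in 4.1 and 7.2, and with the opening of its own sentence.
2. On the window, the AE rule in 7.1.1 and the cited SAE definition differ only in whether performance diagnostics are named. The wide gap is between that definition and the protocol's own SAE list. Both stand in 7.1.2 and both apply to SAEs, so an intended difference between AEs and SAEs does not explain it.
3. Section 7.2 does not settle the window, because its wording can mean the exercise sessions or the whole 12-week period.

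**Test cases**

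- *Unscheduled overnight admission in week 6, outside a session and thought unrelated.* Own list in 7.1.2: SAE. Cited definition in 7.1.2: not an SAE. Section 7: not documented. Section 4.1: not asked about. Section 7.2: depends on the reading.
- *Dizziness during a session, attributed to another illness.* Section 7.1.1: recorded as an AE. Sections 4.1 and 7.2: asked about. Section 7: not documented.
- *Nausea during the 6-minute walk test.* Section 7.1.1: recorded as an AE. The clause in Section 7 concerns home training, and 7.2 names no route for test visits.

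The first two cases change status according to the sentence followed. The third shows that the documentation section does not say where an event counted by 7.1.1 is to be collected.

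**The case against.** The strongest reply is that Section 7 is introductory. Its sentence starts from any incident, and the sections that define and collect events (7.1.1, 7.1.2, 7.2) carry no relation condition, nor does 4.1. On this view there is one loose clause, and a trained therapist would follow 7.2. Part of this stands: a reader might infer that the Protocol records only related incidents, and it never says so. But the clause is the one place in Section 7 that says what is documented on the call, and nothing ranks it below the others. The conflict inside 7.1.2 remains in any case.

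The Protocol also says, in 7.1, that exercise oncology defines adverse events differently from drug trials. That can justify a narrow window. It cannot justify two windows for the same event type.

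Four stronger readings are tempting and are not supported:

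- *An admission the night after a session is filtered out by Section 7.* That clause turns on presumed relation, not timing, and such an admission could well be thought related. Its status is uncertain because of the windows in 7.1.2.
- *The gap can be sized from exposure time.* With exactly three exercise days, the recommended training in Section 4.5 is 3 × 15 + 2 × 30 = 105 to 3 × 30 + 3 × 30 = 180 minutes of a 10,080-minute week, a clock-time ratio of 96 to 56. But Section 4.5 sets three days as a minimum. Seven days give 7 × 30 + 3 × 30 = 300 minutes and a ratio of about 34, and Section 7 leaves volume to the participant. The ratio is clock time, not events, and says nothing about the relation condition.
- *The therapist makes the relation judgement, and the events are lost for good.* The sentence does not say who judges. Section 4.1 has the call cover well-being as well, and reasons for discontinuation are collected, so some traces may survive.
- *Events at test visits are not captured.* Section 7.1.1 says they are recorded, and the test form and telephone log are appendices that are not shown. What can be said is that 7.2 names no route for them.

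**Conclusion.** The contradiction is on the face of the text and needs no outside source. It has two parts: a relation condition in Section 7 that 7.1.1 and 7.1.2 rule out, and two SAE windows within 7.1.2 that 7.2 does not resolve. Sites following different sentences would report different counts from the same events, and the relation condition can only lower the count.

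The size cannot be computed, because no event rates are given. The reach is limited: adverse events are collected as data on the intervention and are not among the listed primary or secondary outcomes, so no listed outcome, hypothesis test or sample size changes. What is affected is the descriptive safety count and its comparability between sites. The conclusion assumes that the appendix forms, which are not shown, do not already impose a single rule. Even if they do, the Protocol text would still contradict itself. The point deserves correction, because the count is the study's safety evidence and missing records may not be recoverable.

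**What to change.** 1. Delete the relation condition from the documentation clause in Section 7.
2. Reconcile Sections 4.1, 7, 7.1.1, 7.1.2 and 7.2 to one capture rule, covering the weekly calls and the test visits.
3. State one time window for AEs and one for SAEs. For SAEs, say which of the two windows in 7.1.2 governs and whether follow-up falls inside it, and replace the ambiguous phrase in 7.2. Without this step, removing the relation condition leaves the main ambiguity in place.
4. Record presumed relation to training, and occurrence during training or testing, as two separate fields, so that neither decides whether an event is written down.
5. Report total and training-related counts separately.

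The cost is protocol wording and, if the forms lack them, two tick boxes in the telephone log and the test form. Some unrelated events will be added, so the total will look slightly less favourable. The separate training-related count keeps the narrower picture available.
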